### Economic evaluation

Micro-costing methods are used to estimate the financial and economic costs of setting up, maintaining and running the social franchise. Micro-costing methods using a bottom-up approach that record resource utilisation at the individual service level are employed to assess the cost of services [41, 42]. Three levels of costs are assessed: (i) costs incurred by the franchisor to plan, initiate and run the social franchise; (ii) costs of activities supporting the social franchise; and (iii) costs to the franchisees of participating in the network and providing the franchise services they offer. Data are obtained through administrative records, interviews with the franchisor, interviews with franchisees and informal observations. Costs are then classified according to: (i) start-up, defined as the initial costs related to the set-up of the social franchise; (ii) capital, defined as the costs of inputs that last for more than 1 year, to be annualised using standard methods [43]; and (iii) recurrent, defined as the costs of inputs that are incurred on a regular basis.

Effectiveness data is drawn from the impact evaluation. Since the study is not powered to measure the impact on mortality, it is necessary to model from the multiple study outcomes to the final health outcomes of deaths and disability adjusted life years (DALY) averted. This is based on a decision-tree model to be developed in light of a review of existing modelling tools such as the Lives Saved Tool (LiST) and Impact 2 [44, 45]. Cost-effectiveness ratios are presented as the cost per death averted and cost per DALY, comparing the situation with and without the social franchising programme. A number of commonly used thresholds are used for assessing whether the results can be considered “cost-effective” [46, 47]. A probabilistic sensitivity analysis using Monte Carlo simulation is conducted to test the effect of uncertainties across model parameters [48].

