### Social franchise model

The Sky franchise network includes providers at various levels. SkyCare is the lowest level of the network and consists of informal rural health providers who are typically medically unqualified. SkyCare providers pay a franchise joining fee to the franchisor and receive signage, posters, training manuals and the ability to phone into a central medical facility. The franchisor maintains the central medical facility by employing qualified doctors to conduct remote medical consultations. SkyCare franchisees are given financial incentives by the network to make antenatal care referrals to SkyHealth franchisees. The second level of the network is SkyHealth. These providers are typically qualified traditional medical practitioners trained to provide Ayurvedic, Yoga & Naturopathy, Unani, Siddha and Homoeopathic care (AYUSH). SkyHealth offers telemedicine services and receive financial incentives for completing three antenatal care consultations with a client. At the highest level, nine franchised clinics and three franchisor-owned clinics are staffed by physicians to provide safe delivery and emergency obstetric care.

The programme provides clinical training to private and public sector health providers. The franchisor trains SkyCare in how to conduct mobile phone consultations. SkyHealth is trained to provide antenatal care, recognise and stabilise pregnancy complications, facilitate timely referrals and provide family planning methods and postpartum contraception counselling. Providers from franchised clinics receive training on national and international guidelines to provide emergency obstetric care, general family planning and postpartum intrauterine devices. Public sector providers with the remit of dealing with emergency obstetric cases also receive clinical training in order to manage linkages and referrals from the private sector. Training in the public sector extends to Accredited Social Health Activist (ASHA) working at the community level. An additional file details the training programme by type of provider [see Additional file 1].

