### Empirical analysis

The impact evaluation relies primarily on the household data. We use a difference-in-difference strategy to estimate impacts [34]. This involves a comparison of changes in the outcomes over time between the intervention and the comparison groups. The analysis exploits the longitudinal nature of the data generated by the recall period used in the two rounds of the household survey and information on the precise timing of the introduction of social franchising in each study area. Specifically, using individual level data, we regress each outcome on a dummy variable indicating whether social franchising has been introduced in the area at the time of birth, area fixed effects and quarter year fixed effects. Unadjusted estimates are reported as well as those that adjust for household characteristics. Controls for household characteristics include below the poverty line status, urban residence, religion, ethnicity, maternal education, parity, multiple birth and the recall period. We cluster the standard errors at the area level.

We test whether the social franchising model has an effect in two ways: the first analysis compares intervention areas with the two sets of comparison areas pooled together, and the second analysis compares the intervention areas with the comparison areas in adjoining districts without social franchising. The latter may arguably be less prone to selection bias since comparison areas in neighbouring districts are beyond the geographical reach of the project and may offer a more credible counterfactual. If the social franchising model is found to have an effect on any of the main outcomes, we conduct subgroup analyses with respect to below the poverty line status, maternal education and caste. Finally, to assess the so-called parallel trends assumption that underpins the difference-in-difference approach, we exploit the recall period in the household data to verify that trends in each of the outcomes are similar between the three study arms before the introduction of the social franchising model. Evidence of diverging pre-trends would be a cause for concern. Baseline outcomes and characteristics of women are also summarised for each study arm with continuous variables presented as mean (standard deviation) and categorical variables by frequencies (percentage). An additional file describes the empirical strategy of the impact evaluation in further detail [see Additional file 4].

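### The with-versus-without-programme cost-effectiveness ratio draws on effects of a local franchisee only; no contrast estimates benefit elsewhere in the programme districts, so the ratio may be mis-scaled

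*Protocol article*

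**What the plan says.** **Costs.** Under Economic evaluation, the article assesses three levels of cost: "costs incurred by the franchisor to plan, initiate and run the social franchise", "costs of activities supporting the social franchise", and "costs to the franchisees of participating in the network and providing the franchise services they offer". It states no restriction to areas with a franchisee.

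**Counterfactual.** The same section presents cost per death averted and per DALY, "comparing the situation with and without the social franchising programme".

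**Effect.** "Effectiveness data is drawn from the impact evaluation". A decision-tree model, still to be developed, then converts the study outcomes to deaths and DALYs.

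**What the impact evaluation estimates.** Under Empirical analysis, exposure is "a dummy variable indicating whether social franchising has been introduced in the area at the time of birth". Study design defines the area as a census ward or village. Two effect comparisons are named: "the first analysis compares intervention areas with the two sets of comparison areas pooled together", and the second sets intervention areas against the neighbouring districts alone. All three arms are compared with each other only for trends before introduction.

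**Arms.** Group A (60 clusters) has a franchisee. Group B (60) has none but lies in the same three districts. Group C (60) lies in neighbouring districts without the network.

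**Reach of the programme.** Under Social franchise model, "The programme provides clinical training to private and public sector health providers". ASHAs are trained too, nine franchised and three franchisor-owned clinics offer delivery and emergency obstetric care, and SkyMeds go out through shops and pharmacies as well as franchisees.

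**The concern.** The costs and the counterfactual refer to a programme running across three districts. The effect refers to a franchisee in one's own ward or village. These fit together only if the programme does nothing for women elsewhere in the districts, or if benefit there is estimated separately.

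Several components could plausibly reach Group B: 12 clinics in districts of 8.1 million people, trained public-sector staff and ASHAs, and medicines sold in ordinary shops. The plan recognises contamination but answers it with a 0.5 km buffer, which does not address these routes. Under the exposure definition, a Group B birth before any local franchisee arrives counts as unexposed. The pooled comparison therefore subtracts part of any Group B benefit from the effect, and neither named contrast measures that benefit.

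Cost-effectiveness is the third study objective and is to be judged against thresholds. A scaling error of severalfold could change that judgement.

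**Working it through.** The article gives no cost-effectiveness figure to reproduce, and neither of the two quantities that drive the size. The ranges below are assumptions.

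**Inputs**
- f = share of the three districts' births in franchisee areas. Not in the documents; assumed 0.10 to 0.75.
- r = benefit per birth in other areas of those districts, divided by benefit per birth in franchisee areas, both relative to Group C. Not in the documents; assumed 0 to 0.5.
- Programme-wide cost is the same in every version, and deaths averted are taken as proportional to the effect.
- A against C is taken as unbiased. B and C have equal weight in the pooled comparison (60 of 120 clusters each).

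**Formulas** (local effect set to 1)
- True total benefit: f + (1 − f)r.
- Benefit credited from A against C: f if applied to franchisee areas only; 1 if applied to all district births.
- The pooled contrast returns 1 − r/2, so the credited benefit becomes f(1 − r/2) or (1 − r/2).
- Reported ÷ true cost per death averted = true benefit ÷ credited benefit.

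**One case in full.** Take the 8-point difference from the sample size section as an illustrative local effect, with r = 0.25 (2 points elsewhere) and f = 0.25.
- True mean benefit: 0.25 × 8 + 0.75 × 2 = 3.5 points.
- A against C, franchisee areas only: 0.25 × 8 = 2.0 credited; 3.5/2.0 = 1.75.
- A against C, all births: 8 credited; 3.5/8 = 0.44.
- Pooled effect: 8 − 2/2 = 7 points. Franchisee areas only: 3.5/1.75 = 2.0. All births: 3.5/7 = 0.50.

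**Reported ÷ true cost per death averted**

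| r | f | A v C, franchisee areas | A v C, all births | Pooled, franchisee areas | Pooled, all births |
|---|---|---|---|---|---|
| 0 | 0.10 | 1.00 | 0.10 | 1.00 | 0.10 |
| 0 | 0.75 | 1.00 | 0.75 | 1.00 | 0.75 |
| 0.25 | 0.10 | 3.25 | 0.33 | 3.71 | 0.37 |
| 0.25 | 0.25 | 1.75 | 0.44 | 2.00 | 0.50 |
| 0.25 | 0.75 | 1.08 | 0.81 | 1.24 | 0.93 |
| 0.5 | 0.10 | 5.50 | 0.55 | 7.33 | 0.73 |
| 0.5 | 0.75 | 1.17 | 0.88 | 1.56 | 1.17 |

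Crediting A against C to franchisee areas only is exact at r = 0 and too high otherwise. Applying it to all births is too low throughout the assumed range (0.10 to 0.88). The pooled contrast recovers 87.5% of the local effect at r = 0.25 and 75% at r = 0.5.

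**Precision of a B against C estimate.** The plan's own sample size serves as a guide. With rates of 50% and 58%, 20 women per cluster and coefficient of variation 0.2, the variance term is 0.25/20 + 0.2436/20 + 0.04 × (0.25 + 0.3364) = 0.0481. Clusters per arm: 1 + 7.849 × 0.0481/0.0064 = 60.0, so the stated 60 reproduces. The standard error with 60 per arm is √(0.0481/60) = 2.8 points, a 95% interval of about ±5.6 points. A spillover of 2 points would be estimated only roughly. Two rounds and covariates may help, as the article expects of its main analysis.

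**The case against.** A reader might infer that the plan divides whole-programme cost by the Group A effect, so that the ratio is simply wrong. The article does not support that. It does not say which contrast enters the model or which births the effect is applied to, and the decision tree is not yet built. Population scaling is something an article may fairly leave to a fuller economic plan, and Additional file 4, on the empirical strategy, is not shown. Applying A against C to births in franchisee areas is a natural choice and is correct if there is no spillover. If there is spillover, it errs against the programme. The article also describes Group C as the possibly more credible counterfactual, and nothing commits the model to the pooled estimate. No passage supports any particular size of spillover, and the article does not say exactly which public-sector or marketing costs will be charged.

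All of this stands, and it limits the point to a risk. It does not remove it. The article names two ways of testing for an effect, and neither measures benefit in non-franchisee areas of the programme districts. Writing down the missing scaling choice would therefore not be enough: if there is spillover, neither named contrast can deliver the stated with-versus-without comparison.

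A second objection concerns the remedy. Group B is not a sample of all other areas. It was matched to resemble Group A, excludes the 0.5 km buffer where spillover may be strongest, and is expected to gain franchisees in some clusters. This is correct, and the fix has to allow for it.

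**Conclusion.** The point holds as a risk of mis-scaling, not as an established error. Programme-level costs and a programme-level counterfactual are paired with effects of a local franchisee, and no named contrast covers the rest of the programme districts. If the programme benefits Group B areas, cost per death averted or per DALY is too high when A against C is credited to franchisee areas only, and too low when it is applied to all district births. For f from 0.10 to 0.75 and r from 0 to 0.5, the first error runs from none to 5.5 times, and the second gives 0.10 to 0.88 of the true value. The size rests wholly on f and r, which the documents do not give, and on the assumption that the costed components lie outside as well as inside franchisee areas.

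**What to change.** - **Economic evaluation:** name Group C as the without-programme comparator, and state that the estimate against B and C pooled does not enter the model.
- **Empirical analysis:** add a difference-in-difference of B against C as a spillover estimate, limited to Group B births before any franchisee arrives in the cluster. The data are already planned: the article reports almost 12 months of baseline births from the first-round recall.
- **Scaling:** match the population to the costs. Apply A against C to births in franchisee areas. Carry B against C for other programme-district areas through the planned Monte Carlo analysis as one scenario, with zero spillover as another.

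The cost is one further contrast on existing data, plus birth counts by area. The downsides are that the B against C term will be imprecise, and that applying it to all other areas is an assumption which must be stated, because Group B is matched to Group A and excludes the buffer.

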### Research ethics and data management

The evaluation study has been approved by the Public Healthcare Society (PHS) Ethics Review Board in India and the London School of Hygiene & Tropical Medicine in the UK. The study design has also received government clearance from the National Health Mission in the State of Uttar Pradesh.

Informed consent is obtained before administering all surveys. Information sheets are read and given to respondents and written or verbal consent is sought prior to interview. The research activities are unlikely to cause any harm since they involve no invasive procedures or examinations. In this respect, it is important to note that the research team are external; they have no responsibility for the implementation of the project or for the services delivered by health providers in the network. The research activities involving data collection through the household survey and health provider survey are not anticipated to cause any harm. There will be no direct benefit to the study participants. The main cost will be the time given by the interviewees. Some of the interviews with households will involve women whose baby may have recently died. The field workers will be trained to deal with such cases sensitively. The household survey includes a mental health screening questionnaire, known as the K10. In some instances, women with severe depression or mental health disorders may be identified through the use of this tool. In such circumstances, researchers are trained to facilitate referral of the individual to an appropriate source of care that is closest to where the woman lives.

Data from the household and health provider surveys are collected through computer-assisted personal interviews. To the extent possible, privacy is maintained during interviews with participants. The study makes every effort to minimise the risk of breaches of confidentiality, particularly in relation to data management and the linking of datasets. The research intends to link data from different sources at the cluster level. This can only be done by the principal investigators at the time of analysis. The quantitative data are to be made publicly available at the end of the project through an established data repository. The data will not contain any global positioning system (GPS) information, identifiers or names that would allow identification of an individual or cluster. In-depth interviews will be conducted in private to maintain confidentiality. Qualitative data are to be securely kept. Audio files are downloaded onto a password protected computer. Data recorded on paper and audio files will be destroyed after the data are analysed and results are reported. In the reporting of the qualitative data, quotations are anonymised such that it is not possible to identify the individual.

## Discussion

The social franchising model in Uttar Pradesh seeks to increase access to and use of basic obstetric care, emergency obstetric care and family planning services. The approach is novel in its focus on maternal health services, its effort to engage with low level and, in some cases, informal healthcare providers and its use of technology such as telemedicine. Whether such an approach to social franchising represents the way forward to improving utilisation and quality of maternal health services is unclear. The evaluation of this model will thus provide an important contribution to the existing literature.

The study’s contribution to knowledge will be strengthened by certain attributes of the study design. The matched difference-in-difference approach provides better causal inference than that obtained in previous studies of social franchising which have rarely used control groups. The large number of outcomes gives us the opportunity to capture the full range of effects across the continuum of care generated by this multifaceted health system intervention. By accounting for multiple inferences, we deal with the risk of specifying many outcomes. Finally, we complement the impact evaluation with a cost-effectiveness analysis and an examination of the implementation process to understand how the programme worked or failed to work and its potential for scaleup.

The findings will need to be interpreted with several potential limitations in mind. First, we must rely on women to recall delivery care practices during childbirth to come to conclusions as to the impact of the social franchising model on quality of care. Measures of quality that use standardised patients are the gold standard but cannot be used in the case of childbirth [26, 49]. Second, we anticipate issues to do with recall. Some indicators place a heavy burden on the woman’s ability to recollect events up to 2 years ago and are therefore likely to suffer from recall problems. In our adjusted estimates of impact, we control for the recall period and the issue is only a concern for the evaluation insofar as recall bias differs between study arms. Third, we note the potential for bias in our impact estimates given that the offer to join the social franchise network is not randomised. To attempt to limit selection problems, we use matched control areas to provide a credible a counterfactual as possible.

There is a dearth of evidence demonstrating whether market-based approaches such as social franchising can improve care in the private sector. Yet expansion of social franchising models in developing countries has been rapid. There is therefore a critical need for robust evaluations of different social franchising models in a wide range of settings to understand whether they contribute to better population health.

## Abbreviations

ASHA: Accredited Social Health Activist
AYUSH: Ayurveda, Yoga & Naturopathy, Unani, Siddha, and Homoeopathy
DALY: Disability adjusted life years
GPS: global positioning system
JSY: Janani Suraksha Yojana
LiST: Lives Saved Tool
PHS: Public Healthcare Society
